## Abstract

**Introduction:**

The use of remote monitoring technology to manage the care of patients with COVID-19 has been implemented to help reduce the burden placed on healthcare systems during the pandemic and protect the well-being of both staff and patients. Remote monitoring allows patients to record their signs and symptoms remotely (eg, while self-isolating at home) rather than requiring hospitalisation. Healthcare staff can, therefore, continually monitor their symptoms and be notified when the patient is showing signs of clinical deterioration. However, given the recency of the COVID-19 outbreak, there is a lack of research regarding the acceptance of remote monitoring interventions to manage COVID-19. This study will aim to evaluate the use of remote monitoring for managing COVID-19 cases from the perspective of both the patient and healthcare staff.

**Methods and analysis:**

Discharged patients from a large urban teaching hospital in Ireland, who have undergone remote monitoring for COVID-19, will be recruited to take part in a cross-sectional study consisting of a quantitative survey and a qualitative interview. A mixed methods design will be used to understand the experiences of remote monitoring from the perspective of the patient. Healthcare staff who have been involved in the provision of remote monitoring of patients with COVID-19 will be recruited to take part in a qualitative interview to understand their experiences with the process. Structural equation modelling will be used to examine the acceptance of the remote monitoring technology. Latent class analysis will be used to identify COVID-19 symptom profiles. Interview data will be examined using thematic analysis.

**Ethics and dissemination:**

Ethical approval has been granted by the ethical review boards at University College Dublin and the National Research Ethics Committee for COVID-19-related Research. Findings will be disseminated via publications in scientific journals, policy briefs, short reports and social media.

Strengths and limitations of this studyA mixed methods approach will allow for an in-depth examination of the remote monitoring programme for the management of patients with COVID-19.The perspective of both patients and healthcare staff will be examined, allowing for a more thorough evaluation of remote monitoring programmes for the management of COVID-19.The use of structural equation modelling techniques allows us to estimate more accurate parameter estimates in examining the user acceptability of remote monitoring programmes.As this study will use a sample of discharged patients with COVID-19 and healthcare staff from a hospital in Ireland, these findings may not be generalisable to patients and healthcare staff in other nations, or to patients who present with conditions other than COVID-19.This project will use a cross-sectional design; therefore, it will not be possible to infer the temporal ordering among the observed relationships.

## Introduction

SARS-CoV-2, which causes COVID-19, is a virus that, in the majority of clinical manifestations, resembles an influenza-like virus, including similar symptomatology such as cough, headache, fever and taste and smell disturbances.^1^ However, patients with COVID-19 can exhibit heterogeneous symptom presentations with studies reporting varying symptom profiles in terms of symptom type (eg, respiratory, neurologic, gastrointestinal) and symptom severity, depending on factors such as age, sex, hospitalisation, comorbid health conditions and additional risk factors.^2–8^ Moreover, COVID-19 appears to follow a biphasic pattern of illness consisting of an initial early viral response phase, followed by an exacerbated inflammatory second phase.^1 9^ This second phase can be accompanied by respiratory compromise and hypoxia, including in cases whereby the initial phase was relatively mild in terms of symptom presentation.^10^ As such, it is important that patients with COVID-19 are continually monitored to ensure that appropriate interventions can take place in the event of clinical deterioration.

However, since the COVID-19 outbreak, healthcare systems have faced numerous challenges, including the loss of resource, mental and physical strain on patients and staff and staffing shortages due to high levels of COVID-19 among healthcare workers.^11–13^ Moreover, individuals may delay seeking treatment^14^ for other health conditions due to the fear and anxiety of contracting COVID-19, exacerbating health issues and increasing the subsequent burden on the healthcare system.^15^ To effectively protect the well-being of patients and healthcare staff and to prevent the onward transmission of COVID-19, it is imperative that alternative initiatives are implemented to mitigate the impact of the COVID-19 pandemic on healthcare systems. These alternative initiatives may, therefore, allow the limited healthcare resources to be used most efficiently.

One such initiative is the remote monitoring of patients with COVID-19.^16–19^ This is a system that involves the use of devices that allow healthcare staff at one location to monitor a patient at a different location. This allows for the home monitoring of patients, including physiological metrics such as oxygen saturation, body temperature and heart rate,^20^ with mild to moderate symptoms (ie, who do not require hospitalisation) who are in self-isolation, tested positive for COVID-19 and/or are symptomatic. In addition, remote monitoring technology may be useful in monitoring postacute COVID-19 (or ‘long-COVID’), whereby patients continue to exhibit some of the symptoms of COVID-19 despite having recovered.^21 22^ Remote monitoring, as an alternative route for providing healthcare, has previously been found to be a useful and cost-effective means to managing patients across numerous types of conditions.^23–27^ Recent research has demonstrated the feasibility of using remote monitoring technology to prospectively monitor respiratory illnesses such as common human coronaviruses, rhinovirus and respiratory syncytial virus.^28^ However, given the recency of the COVID-19 pandemic, research pertaining to remote monitoring for managing patients with COVID-19 is limited. As such, it is important to examine different aspects of remote monitoring, such as patient and staff experiences and acceptability, to ensure its effectiveness as an alternative means to managing COVID-19 symptoms.

One important aspect to consider is the experience of the technology from the patient’s perspective. Patient experience of the intervention is an important aspect in predicting treatment adherence.^29^ One such means of modelling patient experience and adherence in remote monitoring-based interventions is through the technology acceptance model (TAM).^30^ The TAM posits that the use of technology, such as remote monitoring, is the result of one’s behavioural intention to use the technology. Behaviour intention, in turn, can be explained through one’s perceived ease-of-use, perceived usefulness and attitude towards the technology. Alternative models of user acceptance (eg, the theory of planned behaviour (TPB), the unified theory of acceptance and use of technology (UTAUT) and the task-technology fit (TTF) models^31–33^) similarly posit that the use of the technology is the result of one’s behavioural intention to use the technology. However, in predicting behavioural intention, these models also incorporate factors such as subjective norms/social influences that may play an important role in user acceptance.^31^ These models aid in explaining user acceptance by providing a framework to incorporate psychosocial and behaviour theories such as the TPB^34^ and the UTAUT^35^ and have been applied to remote monitoring interventions across varying patient groups.^36–39^

Although research on remote monitoring for COVID-19 symptoms is scant, users of remote monitoring technologies for COVID-19 symptoms have generally reported high satisfaction and ease-of-use across interventions.^16 17^ Moreover, findings suggest that patient’s use of telemedicine systems can be effectively modelled within the TAM and TPB framework.^13 40 41^ As such, these frameworks may be extended to modelling adherence in remote monitoring for patients with COVID-19.

Recent evidence, although limited, suggests healthcare staff generally have positive experiences with the use of telemedicine during the COVID-19 pandemic and that it may play an important role in their well-being.^42 43^ For example, healthcare staff reported that they felt that the technology was easy to use and were satisfied with the safety precautions implemented to allow them to work from home.^42^ Research indicates that healthcare staff generally hold positive views towards the remote monitoring of patients across numerous conditions.^44^ However, there are notable concerns, such as managing increased workload and reduced quality of care from fewer patient visits.^44 45^ This suggests that further research is required to better understand the staff experience of remote monitoring technology for patients with COVID-19, particularly across a diverse range of healthcare roles.

This project aims to evaluate a remote monitoring intervention for managing COVID-19 cases in a large urban teaching hospital in Dublin, Ireland. The objectives of this project are twofold. First, the acceptance of the remote monitoring technology from the perspective of the patient (objective 1a) and healthcare staff (objective 1b) will be examined using a mixed methods approach. User acceptance from the perspective of the patient will be examined using factors extracted from an integrated model of the UTAUT and TTF models,^33^ while also controlling for a number of covariates, using quantitative analyses. User acceptance of remote monitoring for managing patients with COVID-19 from the perspective of both the patient and healthcare staff will also be examined using a qualitative methodology.

Second, patient symptom profiles of COVID-19 and postacute COVID-19 will be identified using a quantitative method approach (objective 2). Identifying patient symptom profiles of COVID-19 and postacute COVID-19 may highlight potential subgroups of patients who may be more likely to present with higher symptomatology or different sets of co-occurring symptoms. In addition, predictors, such as demographic variables and pre-existing comorbidities, of the COVID-19 symptom profiles will be determined. Identifying these predictors may be of particular benefit to identifying patients who may need to be monitored for a longer duration. For example, identifying patients who are likely to remain symptomatic (particularly symptoms such as shortness of breath) may need to be monitored for a longer duration after acute COVID-19. Furthermore, identifying such profiles may aid COVID-19-positive patients in being prepared for a likely set of symptoms that they may experience long term, depending on the predictors of the COVID-19 symptom profiles. For example, identifying patients who are likely to have persistent symptoms such as fatigue and loss of taste/smell may be useful in helping the patient being prepared for these long-term effects.

## Methods

### Research design

A mixed methods design is proposed to achieve the research objectives of this project. The measures used to collect the data consist of both quantitative measures (eg, user acceptance of the remote monitoring technology) and qualitative interviews (for both patient and staff experience of remote monitoring). Work package 1 will use both quantitative cross-sectional survey data and qualitive interviews to examine patient experiences. Work package 1 will address objectives 1a and 2. Quantitative analyses will be used to determine the acceptance of the remote monitoring technology among the patients and to identify the patient symptom profiles of COVID-19 and postacute COVID-19. Work package 2 will use qualitative interviews to examine healthcare staff experiences. Work package 2 will address objective 1b.

### Participants and recruitment strategy

Participants will consist of patients and healthcare staff recruited from the clinic site. First, patients who have completed their treatment via remote monitoring will be recruited to gather information on their experiences of the intervention in the form of a quantitative survey. Patient recruitment will begin in February 2021 and end in June 2021. A total of 925 patients have been discharged from the remote monitoring service. Patients will be recruited via an email sent through gatekeepers at the clinic site. All patients will receive an email with the participant information sheet and a link to an online survey. A subsample of these patients will also be recruited for a qualitative interview regarding their experiences of remote monitoring. As part of the survey, patients have the option of indicating if they wish to participate in a telephone interview and provide their contact details. Patients who consented to interview will be purposively sampled to get a representative sample based on age, gender and education. These patients will then be contacted by a member of the research team to arrange a suitable time for interview, once 7 days have passed since signing the consent form.

Second, staff who have been remotely monitoring patients with COVID-19 will be recruited via an email sent through gatekeepers at the clinic site. These participants will begin to be recruited in February 2021 and end in June 2021. A total of 25 staff worked in the virtual clinic since it was set up in April 2020. All staff who worked in the clinic will receive an invitation to participate in a qualitative interview regarding their experiences of remote monitoring from a healthcare staff perspective. If they choose to take part, a member of the research team will contact them to schedule a suitable time for a telephone interview, once 7 days have passed since signing the consent form.

The inclusion criteria for this project are that the patient or staff member must (a) be at least 18 years of age, (b) have the capacity to consent, (c) provide their full informed consent to take part in the study, (d) if they are a patient, they must have received a positive COVID-19 diagnosis, (e) if they are a patient, they must have undergone treatment via remote monitoring and (f) if they are a member of staff, they must have been monitoring the data and interacting with patients with COVID-19 for a minimum of 1 week. Patients who did not receive a positive diagnosis for COVID-19 and/or did not undergo treatment via remote monitoring will be excluded. The exclusion criterion for staff members is if they worked at the virtual clinic for less than 1 week.

### Measures: work package 1

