#### User acceptance of remote monitoring equipment

Patients who report using either a pulse oximeter and a remote monitoring phone application, or just the remote monitoring phone application will be asked to complete a 16-item questionnaire pertaining to their experience of the technology. This multidimensional measure is comprised of items relating to the different factors of user technology acceptance, based on a recent integrated model consisting of factors from the UTAUT and TTF models^33^. Several factors will be extracted from this model, consisting of ‘social influence’ (two items; the degree to which important others agree to the use of the technology; for example, ‘people who influence my behaviour thought it was important that I use the remote monitoring equipment’), ‘facilitating conditions’ (three items; individual’s perception of the availability of resources to use the technology; for example, ‘I felt I had the necessary knowledge to use the remote monitoring equipment’), ‘effort expectancy’ (four items; ease-of-use related to using the technology; for example, ‘I find it easy to use such equipment’), ‘performance expectancy’ (four items; effectiveness to users in performing specific tasks; for example, ‘I feel remote monitoring equipment is useful in obtaining health information’) and ‘TTF’ (three items; the degree to which users believe that the performance of the technology matches its intended use; for example, ‘In general, the remote monitoring equipment fully met my needs’). All items will be rated using a five-point Likert scale (‘strongly disagree’=1, ‘strongly agree’=5), with higher scores reflecting greater scores towards its respective factor. Previous psychometric research has supported the validity and reliability of these items.^33^ Participants will also have the opportunity to share any additional information about their experience through an open-ended question.

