#### Adherence to the use of remote monitoring equipment

Adherence to the use of the pulse oximeter throughout the intervention will be assessed via three statements with participants being asked to choose the statement that best reflects their experience (‘I did not use the oximeter’, ‘I tried to use the oximeter but gave up because it was too difficult’, ‘I occasionally used the oximeter during my treatment’ and ‘I used the oximeter consistently during my treatment’). In addition, participants will have the option to share any additional information about their experience of using the device through an open-ended question. Adherence to the use of the remote monitoring phone application will be assessed via three statements with participants being asked to choose the statement that best reflects their experience (‘I did not use the phone application to record my symptoms’, ‘I tried to use the phone application but gave up because it was too difficult’, ‘I occasionally used the phone application to record my symptoms throughout my treatment’ and ‘I used the phone application to record my symptoms consistently throughout my treatment’). In addition, participants will have the option to share any additional information about their experience of using the phone application through an open-ended question.

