#### Patient experience interview

Semistructured interviews will be conducted with patients who have undergone remote monitoring as part of their treatment for COVID-19 (n ≈ 20, or until saturation is reached). These interviews will be conducted by trained interviewers. A topic guide has been designed to explore the patient’s experience of the remote monitoring intervention, including their: experience of having COVID-19; interactions with staff during the intervention; experience of the remote mentoring equipment; opinion on remote monitoring compared with treatment-as-usual and opinions on using remote monitoring for other types of conditions. The interviews will take approximately 20 min. Interviews will be conducted via telephone on loudspeaker and recorded using audio-recorder or via video call on Zoom and the video call recorded to facilitate COVID-19 restrictions.

### Data analysis: work package 1

The first objective will be attained using a mixed methods design. First, descriptive statistics will assess the overall patient self-reported patient–professional interaction, adherence to the use of the remote monitoring equipment and acceptance towards the remote monitoring technology and provide the sample characteristics.

Second, structural equation modelling will be used to examine different aspects of user acceptance towards remote monitoring technology, such as the performance expectancy of the equipment from the perspective of the patient. Structural equation modelling is advantageous as it can parse out measurement error, thereby yielding more accurate parameter estimates^47^ and can be applied to medical research.^48 49^ We will also determine the effect of several exogenous covariates such as demographics, pre-existing comorbidities, prior experience with mobile phone applications and patient–professional interaction in predicting user acceptance towards the use of remote monitoring technology. Given the larger sample size required for structural equation modelling, in the event that an insufficient sample size is gathered, then a multiple regression analysis will be conducted instead.

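### Patient interviewees are sampled on age, gender and education but not on recorded equipment use, so few or no patients who gave up or did not use it may be interviewed.

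*Protocol article*

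**What the plan says.** All places are in the protocol article.

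- **Participants and recruitment strategy.** The survey goes to discharged patients: "patients who have completed their treatment via remote monitoring will be recruited", and "A total of 925 patients have been discharged from the remote monitoring service". Within the survey, "patients have the option of indicating if they wish to participate in a telephone interview". Those who agree are then "purposively sampled to get a representative sample based on age, gender and education". No other selection variable is named.
- **Patient experience interview.** The target is "n ≈ 20, or until saturation is reached". No quota by use of the equipment is set.
- **Introduction.** Objective 1a is patient acceptance of the technology. It is to be examined quantitatively and also qualitatively.
- **Adherence to the use of remote monitoring equipment.** For the oximeter and for the app, the survey offers four answers: not used, tried and abandoned, occasional use, consistent use. (The text announces three statements but lists four; the four listed are used here.) The abandonment option for the app reads "I tried to use the phone application but gave up because it was too difficult". Each device also has an optional free-text question.
- **User acceptance of remote monitoring equipment.** The 16-item questionnaire goes to "Patients who report using either a pulse oximeter and a remote monitoring phone application", or the app alone.
- **Staff experience interview.** Staff are asked, among other things, how patients received the equipment.

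**The concern.** Purposive sampling is most useful when it varies traits that bear on the question. One question here is acceptance, and the Introduction's own theory treats use of a technology as the outcome of the intention to use it. Whether a patient kept using the equipment, dropped it or never started is therefore an informative trait. It is recorded in the same survey in which patients volunteer, so it can be known before anyone is selected. The sampling rule leaves it out.

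What is at stake is the breadth of the qualitative evidence on objective 1a. If those who gave up or did not use the equipment are rare among volunteers, the accounts of barriers would come mainly from people who kept using it. The saturation rule may lengthen interviewing but does not direct it towards the missing group. The word representative also promises more than about 20 purposively chosen volunteers can deliver.

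**Working it through.** The plan gives no figure on this point to reproduce. The check has two parts.

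**1. Can the plan reach these patients by another route?**

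| Route | Who is reached | Limit |
|---|---|---|
| 16-item acceptance questionnaire | Patients who report using the app, with or without the oximeter | Patients who never used the app are not routed to it; for those who tried and gave up, the text does not settle it |
| Free text after the adherence items | Not restricted to users | Optional, and not an interview |
| The gave-up response option | Patients who abandoned a device | Gives one fixed reason, difficulty |
| Staff interviews | Staff impressions of how patients received the equipment | Second-hand |
| Patient interviews | Volunteers balanced on three demographics | Nothing steers selection to this group |

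**2. How likely is it that the interviews miss the group?**

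Inputs:

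- n = 20 interviews, from Patient experience interview.
- p = share of volunteers who gave up on or did not use the equipment. **Assumed**, because the documents do not give it; range 2% to 30%.
- Selection on age, gender and education is assumed unrelated to p.

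Formulas: expected number = 20p; P(none) = (1 − p)^20; P(at most one) = (1 − p)^20 + 20p(1 − p)^19.

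| p | Expected number | P(none) | P(at most 2) |
|---|---|---|---|
| 2% | 0.4 | 0.98^20 = 0.668 | 0.993 |
| 5% | 1.0 | 0.95^20 = 0.358 | 0.925 |
| 10% | 2.0 | 0.90^20 = 0.122 | 0.677 |
| 20% | 4.0 | 0.80^20 = 0.012 | 0.206 |
| 30% | 6.0 | 0.70^20 = 0.001 | 0.035 |

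P(at most one) is 0.736 at 5% and 0.392 at 10%.

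Share needed for a 95% chance of at least one such interviewee: 1 − 0.05^(1/20) = 0.139, about 14%.

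Finite-pool check (hypergeometric; pool sizes assumed, since the number of volunteers is not given). At a 10% share, P(none) is 0.067, 0.095 and 0.109 for pools of 50, 100 and 200. At 5% it is 0.319 and 0.340 for pools of 100 and 200; with 2 such patients in a pool of 50 (4%) it is 0.355. The picture does not change.

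If adherence category were a criterion, with at least one interviewee per category wherever one consents, P(none) would be zero whenever the pool contains such a patient.

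**The case against.** The strongest reply is that sampling on age, gender and education is an ordinary qualitative choice and contradicts nothing else in the article. The interview also covers more than acceptance: the illness itself, contact with staff, comparison with usual care, and other conditions. Demographic spread suits that scope. This stands, and it is why the point is an improvement and not an error. It does not remove the point, because the article states the selection rule outright and so does not merely leave it to a fuller document.

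Three stronger readings are tempting and are not supported:

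- *That the interviews are the only or main place where non-users can be heard.* The free-text questions are not limited to users, and staff are asked how patients received the equipment. These routes are thinner than an interview, but they exist.
- *That everyone who abandoned the equipment is shut out of the acceptance questionnaire.* The routing text establishes this only for patients who never used the app. A patient who tried it and gave up may well report having used it.
- *That adherence defines the research question, so that the conclusion will be tilted towards acceptance.* Acceptance and adherence are measured separately, and a consistent user can still find the equipment hard to use or poorly suited. Nothing shows that saturation would be declared early.

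The probabilities are also open to challenge. The share is assumed, a binomial model describes random and not purposive selection, and the risk almost vanishes at 20% or more. If use varies with age or education, balancing on those may itself bring in some non-users; the planned analysis does treat demographics as possible predictors of acceptance. In the other direction, patients who struggled with the technology may be less likely to answer an emailed online survey or to volunteer, which would lower their share. The figures are an illustration of risk, not an estimate.

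**Conclusion.** The point holds as a low-cost improvement to a stated rule. Patient interviewees are selected from volunteers on three demographic variables, while an acceptance-relevant variable already collected in the same survey goes unused. The interviews may therefore include few or no patients who gave up on or did not use the equipment.

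The size depends on a share that the documents do not give. If it is unrelated to the three criteria, the chance that 20 interviews include none is about 36% at 5%, 12% at 10% and 1% at 20%. The concern is real if such patients are uncommon among volunteers and nearly disappears if they make up a fifth or more. It bears on the breadth of the qualitative evidence for objective 1a and does not affect the quantitative analyses.

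**What to change.** In Participants and recruitment strategy:

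1. Add self-reported adherence category, for the app and for the oximeter, as a purposive sampling criterion beside age, gender and education.
2. Approach volunteers in the gave-up and not-used categories first.
3. Describe the sample as maximum variation, not representative.
4. Report interviewees by adherence category.
5. If nobody in a category volunteers, state this as a limitation of the acceptance conclusion. Do not make interviewing every category a condition for saturation, since that condition could not be met if no one volunteers.

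It would also help to say whether patients who tried the app and gave up receive the 16-item questionnaire.

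Cost: no new survey item and no additional interviews. It needs the same link between survey answers and volunteers that the demographic criteria already require. The downside is slightly less freedom to balance the demographic criteria.
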